## 9.4 Statistical Analyses

### 9.4.1 General Approach

We will first conduct descriptive and graphical analyses to check for outlier and abnormal values, verify that distribution of measures meets assumptions of planned statistical tests, and explore the success of randomization. Primary analyses for all aims will be intent-to-treat analyses of data from baseline to week 8, based on group allocation. Secondary analysis will be done removing patients who do not complete at least 4 weeks on study as well as any patients whose urine samples show presence of cannabinoid metabolites other than THC or whose pill counts reveal they took less than 50% of the reported optimized dose.

Statistical analysis will be done assuming all data is non-normal. Continuous data will be described as means and quartiles, categorical data will be described as percentages.  All inferential tests will be two-tailed.

### 9.4.2 Analysis of the Primary Efficacy Endpoint(s)

We will examine change in pain and quality of life measures from each participant’s own baseline after 8 weeks of treatment (difference in differences analysis). Median change from baseline of patients on dronabinol will be compared to median change from baseline of patients on placebo. We have chosen to compare change from baseline between the two groups to account for heterogeneity in cause and severity of chronic pain at baseline seen in people with SCD. Comparisons of change from baseline to end of study between patients on placebo and dronabinol will be done using a Rank Sum test. A backward stepwise multivariate regression analysis will be performed to assess for covariates associated with the primary and secondary outcomes.  As the group size will be small a regression analysis will also be done to assess if any covariates associated with the outcomes are significantly difference between the study groups.

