## 1.2 Schema

## 1.3 Schedule of Activities (SoA)

| **Related Aim** | **Related Skill** | **Form** | **Measure** | **Baseline** | | **Week 2** | | **Week 4** | | **Week 6** | | **Week 8** | |
| --- | --- | --- | --- | --- | --- | --- | --- | --- | --- | --- | --- | --- | --- |
| 1 | 1,2,4 | survey | PROMIS Pain Impact | X | |  | | X | |  | | X | |
| 1 | 1,2,4 | survey | ASCQ-Me Pain Impact | X | |  | | X | |  | | X | |
| 1 | 1,2,4 | survey | LANSS Scale | X | |  | |  | |  | | X | |
| 1 | 1,2,4 | survey | PROMIS Pain Quality Neuropathic | X | |  | | X | |  | | X | |
| 1 | 1,2,4 | survey | PROMIS Pain Quality Nociceptive | X | |  | | X | |  | | X | |
| 1 | 1,2,4 | EMR | Daily Opioid Use (OME) | X | |  | | X | |  | | X | |
| 1 | 1,2 | survey | Self Reported Episodes of Pain Crisis | X | |  | | X | |  | | X | |
| **Quality of Life Related Outcomes:** | | | | |  | |  | |  | |  | |  |
| 1 | 1,2 | survey | ASCQ-Me Stiffness | X | |  | | X | |  | | X | |
| 1 | 1,2 | survey | ASCQ-Me Sleep Impact | X | |  | | X | |  | | X | |
| 1 | 1,2 | survey | ASCQ-Me Emotional Impact | X | |  | | X | |  | | X | |
| 1 | 1,2 | survey | ASCQ-Me Social Impact | X | |  | | X | |  | | X | |
| **Inflammatory Markers:** | | | | | | |  | |  | |  | |  |
| 2 | 1,2,3 | blood | White Blood Cell Count | X | |  | | X | |  | | X | |
| 2 | 1,2,3 | blood | Absolute Neutrophil and Monocyte Count | X | |  | | X | |  | | X | |
| 2 | 1,2,3 | blood | Substance P | X | |  | | X | |  | | X | |
| 2 | 1,2,3 | blood | Tryptase |  | |  | |  | |  | |  | |
| 2 | 1,2,3 | blood | Pro Inflammatory: IL1-b, TNFα, IL-6, VCAM-1 | X | |  | | X | |  | | X | |
| 2 | 1,2,3 | blood | Anti Inflammatory: IL4, IL10 | X | |  | | X | |  | | X | |
| **Safety and Tolerability** | | | | |  | |  | |  | |  | |  |
| 3 | 1 | survey | PROMIS Anxiety | X | |  | | X | |  | | X | |
| 3 | 1 | survey | PROMIS GI Nausea and Vomiting | X | |  | | X | |  | | X | |
| 3 | 1 | survey | PROMIS Cognitive Function | X | |  | | X | |  | | X | |
| 3 | 1 | CRA | Self-Reported Adverse Effects | X | | X | | X | | X | | X | |
| 3 | 1 | EMR | Hospital Utilization (ER/Admissions) | X | |  | | X | |  | | X | |
| 3 | 1 | urine | Urine Pregnancy Test | X | |  | | X | |  | | X | |
| 3 | 1 | blood | BMP and liver tests | X | |  | | X | |  | | X | |
| **Other:** | | | | |  | |  | |  | |  | |  |
| 1 | 1 | urine | Urine Toxicology | X | |  | | X | |  | | X | |
| 1 | 1 | CRA | pill count | X | |  | | X | |  | | X | |

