# 8 Study Assessments and Procedures

## 8.1 Efficacy Assessments

Informed consent will be obtained prior to screening activities. Screening may take multiple visits but must be completed within 30 days of obtaining informed consent. The following assessments will be completed:

- Written Informed consent
- Demographics
- Medical history - Including SCD type, SCD related problems, other medical problems, psychiatric and substance use history, description of pain and pain treatment
- Weight
- Vital Signs
- Review of current and past medications
- Pregnancy test - For women of child bearing potential Urine or serum.
- Urine test for cannabinoids
- Physical exam
- Baseline Patient Reported Outcomes (ASCQ-Me survey domains for pain impact, emotional impact, social impact, stiffness, and sleep, PROMIS domains for pain impact, neuropathic pain, nociceptive pain, cognitive function, gastrointestinal distress and anxiety. LANSS, PQ-B, C-SSRS)

Data will be collected from five sources: 1) Validated patient reported outcome surveys at baseline, and weeks 4 and weeks 8; 2) Timeline Follow-Back for hospital utilization use at research visits at weeks 4 and 8; 3) medical interview and physical examination at screening, weeks 4 and weeks 8; 4) laboratory markers of inflammation including IL1b, IL4, IL6, IL10, VCAM-1 and TNFα, tryptase, and substance P at baseline, weeks 4 and weeks 8 5) urine toxicology tests at baseline and weeks 4 and weeks 8, 6) safety laboratory tests of renal function, liver function, complete blood count and reticulocytes and pregnancy at screening and at weeks 4 and weeks 8;

In-person screening research interview, screening medical interview and physical examination data will be recorded on paper data collection instruments that identify participants only by unique study ID number. Patient reported outcome surveys will be performed on an I-Pad and entered automatically into REDCap. Data will be entered into a password-protected, encrypted web-based REDCap database, and paper documents will be filed in a locked cabinet.

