### 8.4.3 Reporting Unanticipated Problems to Participants

# 9 Statistical Considerations

## 9.1 Statistical Hypotheses

- Primary Efficacy Endpoint(s):

Hypothesis: Participants who receive dronabinol will have an improvement in pain impact (primary outcome) at 8 weeks compared to patients who receive placebo.

- Secondary Efficacy Endpoint(s):

Hypothesis: Participants who receive dronabinol will have improvements in other measures of pain (average daily opioid use, neuropathic and nociceptive pain severity, health care utilization, and self-reported episodes of pain crisis) and quality of life (stiffness, sleep, emotional impact, and social impact) at 8 weeks compared to participants who receive placebo.

Hypothesis: Patients who receive dronabinol will have an increase in anti-inflammatory markers (IL4, IL10) reduction in pro-inflammatory markers (all others) at 8 weeks compared to patients who receive placebo.

Hypothesis: Participants in the dronabinol group will report greater incidence of low-grade adverse events such as dizziness or nausea but no greater serious AEs (cognitive function) compared to participants in the placebo group.

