### 9.4.3 Analysis of the Secondary Endpoint(s)

To account for inter-patient heterogeneity, our primary comparison will be to use a difference in differences analysis to examine change from their own baseline after 8 weeks of treatment with dronabinol. Comparisons of changes in WBC with differential, CRP, tryptase, substance P, and cytokines from baseline to end of study between patients on placebo and dronabinol will be done using t-tests or Wilcoxon rank-sum tests. A backward stepwise multivariate regression analysis will be performed to assess for covariates associated with the primary and secondary outcomes. As the group size will be small a regression analysis will also be done to assess if any covariates associated with the outcomes are significantly difference between the study groups.

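### Pain crises and hospital use are event counts, but the only analysis that reaches them is a baseline-to-end change score, and the two stated sources for hospital use disagree on whether a baseline exists

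*Protocol*

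**What the plan says.** **Role of the outcomes.** The secondary efficacy hypothesis in Protocol 9.1 lists "health care utilization, and self-reported episodes of pain crisis" with opioid use and pain severity as measures of pain expected to improve at 8 weeks.

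**Analysis.** Section 9.4.2 covers pain and quality-of-life measures together as change from each participant's own baseline, and specifies the test: "Comparisons of change from baseline to end of study between patients on placebo and dronabinol will be done using a Rank Sum test". Section 9.4.3 takes the same approach to secondary endpoints: "our primary comparison will be to use a difference in differences analysis to examine change from their own baseline after 8 weeks of treatment with" the study drug. The stepwise regression in both sections looks for associated covariates and is not the treatment comparison. The Fisher tests in 9.4.4 apply to individual adverse events and mention neither outcome.

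**Collection.** The Schedule of Activities (1.3) has a survey item, "Self Reported Episodes of Pain Crisis", and an EMR item, "Hospital Utilization (ER/Admissions"), each at baseline, week 4 and week 8. Neither has a recall or look-back window. Section 8.1 instead lists, for hospital use, "Timeline Follow-Back for hospital utilization use at research visits at weeks 4 and 8".

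**The concern.** End value minus baseline value suits a survey score, which describes a state at the visit. A crisis or an admission is an event that accumulates over time, so its count means something only with the window it covers. Without stated windows, a change score can leave out on-treatment events or subtract counts from windows of unequal length. Even with matched windows, it adds the full noise of one short baseline count to the outcome.

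A real reduction in crises or admissions would then be more likely to be missed, and individual values could have the wrong sign. For hospital use there is a further problem: if data are collected as 8.1 describes, the change score cannot be computed.

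**Working it through.** **1. The plan's own figure.** Protocol 9.2 uses a difference of 5, SD 6.5, two-sided alpha 0.05 and 80% power. The normal approximation, n = 2(1.96 + 0.84)² × 6.5² / 5², gives 27 per arm. With the noncentral t, power is 79.2% at 27 and 80.7% at 28, so the stated 28 reproduces. Allowing 20% attrition, 56 / 0.8 = 70. These figures concern the primary endpoint and are not affected here. The protocol gives no event rate or power for crises or hospital use.

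**2. What the change score does to a count.** Take a participant with 1 crisis in a 4-week baseline, 2 in weeks 1-4 and 0 in weeks 5-8.
- Visit-to-visit recall: 0 − 1 = −1, an apparent improvement.
- Week 8 recall over all 8 weeks, baseline over 4: 2 − 1 = +1, an apparent worsening.
- As rates: 2 events in 8 weeks is 1 per 4 weeks, the same as baseline.

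The sign depends on windows that the protocol does not state. Under visit-to-visit recall, the on-treatment time used is 4 of 8 weeks, or 50%.

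**3. Size of the loss.** All event inputs are assumptions. Each participant has a gamma multiplier g (mean 1, variance d). Counts in three 4-week windows are Poisson with mean m·g, multiplied by 0.5 on dronabinol in the two treatment windows. There are 28 per arm, no dropout, and 2,000 simulated trials per setting. Let B, W4 and W8 be the window counts. The count model is quasi-Poisson: log E(W4 + W8) = a + b·arm + c·log(B + 0.5).

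| m per 4 weeks | d | Rank Sum, W8 − B | Rank Sum, W4 + W8 − 2B | Rank Sum, W4 + W8 | Count model |
|---|---|---|---|---|---|
| 0.25 | 0.5 | 10% | 13% | 27% | 26% |
| 0.25 | 1 | 9% | 13% | 22% | 21% |
| 0.5 | 0.5 | 16% | 20% | 40% | 44% |
| 0.5 | 1 | 15% | 19% | 31% | 39% |
| 1 | 0.5 | 25% | 32% | 55% | 65% |
| 1 | 1 | 24% | 30% | 39% | 58% |
| 2 | 0.5 | 44% | 53% | 70% | 88% |
| 2 | 1 | 44% | 53% | 48% | 83% |

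With a rate ratio of 1, the W8 − B Rank Sum rejects in 4.1% to 5.3% of trials.

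Repeating this for m from 0.5 to 2 with d of 0.3 and 0.8 gives about 14-46% for W8 − B, 18-58% when only the week 4 events are restored, and 42-95% for the count model. The top of the last range moves by a few points between runs. Restoring week 4 alone therefore adds about 4 points (18 − 14) to 12 points (58 − 46). The rest of the gain comes from not subtracting the baseline count and adjusting for it instead.

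**4. The two sources for hospital use.**

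| Place | Source | Baseline | Week 4 | Week 8 |
|---|---|---|---|---|
| Schedule of Activities (1.3) | EMR | yes | yes | yes |
| Section 8.1 | Timeline Follow-Back | no | yes | yes |

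They differ on source and on whether a baseline exists. Pain crises have one source, the survey, with a baseline.

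**The case against.** **Week 4 events may not be lost.** A reader might infer that the plan discards them. The documents do not say so: a week 8 report covering all 8 weeks would include them. This objection stands, so the loss is conditional on the recall window. Window definitions can be left to an SAP. The criticism here is of the analysis the protocol does fix, and the inefficiency remains with matched windows.

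**These are not two listed secondary endpoints.** Also correct. Pain crises appear only in the 9.1 hypothesis and the Schedule of Activities. Hospital use is in the synopsis list beside safety items, is absent from Section 3, and sits under safety in the Schedule. But 9.1 names both as efficacy measures of pain, and no other section gives them an analysis.

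**The power gap can be overstated.** Comparing week 8 minus a 4-week baseline with an 8-week total minus an 8-week baseline gives 26-27% against 45-48% at 1 event per 4 weeks. That comparison doubles the baseline window as well, so it is not the cost of dropping week 4, which is the smaller amount above.

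**Within-person change has a rationale.** Section 9.4.2 cites baseline heterogeneity. That is a fair reason to use the baseline; a covariate does so at less cost in noise. At 2 events per 4 weeks and d = 1, an unadjusted total gains little over the change score (48% against 44%), so baseline should not simply be dropped.

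**Source mixing is not planned.** A reader might infer that an EMR count will be subtracted from a self-report, or that hospital use has no baseline at all. No section says the former, and the Schedule contradicts the latter.

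**Conclusion.** The point holds as a matter of efficiency and definition. The test remains valid: type I error is near 5%, and the primary endpoint and sample size are untouched. For two event-count outcomes that 9.1 names as efficacy measures, the stated comparison is a poor choice. The power figures rest on assumed event rates, a rate ratio of 0.5, gamma-Poisson counts, visit-to-visit 4-week windows and no dropout. At 0.25 events per 4 weeks every method is weak (27% at best), and the count model does no better than a Rank Sum test on the total.

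The conflict between 8.1 and the Schedule of Activities needs no assumption. Under 8.1 the hospital-use change score has no baseline to subtract. It should be settled before data collection, because an interview not taken at baseline can only be reconstructed later.

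**What to change.** 1. For pain crises and ER/hospital use, define the outcome as the total count from first dose to week 8: the week 4 and week 8 reports added over non-overlapping windows.
2. Compare arms with an overdispersed count model (quasi-Poisson or negative binomial), with observed time as offset and the baseline count as covariate. The offset lets participants who leave early contribute the time they were observed.
3. State the recall window for each report and the baseline look-back. As a covariate, the baseline need not cover 8 weeks.
4. Reconcile 8.1 with the Schedule of Activities so that one source serves hospital use at baseline, week 4 and week 8.
5. Keep change scores for the survey scales.

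**Cost.** Protocol wording only if the EMR is used throughout, since the Schedule already has it at all three time points. If Timeline Follow-Back is preferred, it adds one interview at the existing baseline visit. The small downside is reliance on a count model in a small sample.

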# 3 Objectives and Endpoints

| OBJECTIVES | ENDPOINTS | JUSTIFICATION FOR ENDPOINTS |
| --- | --- | --- |
| Primary | | |
| Patient Reported Outcome Information System (PROMIS, a non-disease specific patient reported outcome survey system) pain impact score | Change from baseline to end of week 8 | The primary outcome is the PROMIS pain impact score, which assesses not only the severity of the pain but the impact of the pain on the participant’s daily living, a more relevant patient-centered outcome. PROMIS pain impact score has been validated as a onetime measure in people with SCD, and further has been validated to detect changes over in other diseases of chronic pain.^63,64^ |
| Secondary | | |
| Other Patient Reported Outcomes (ASCQ-Me survey domains for emotional impact, social impact, stiffness, and sleep) PROMIS domains for neuropathic pain, nociceptive pain, cognitive function, gastrointestinal distress and anxiety.^66^ LANSS, PD-B, C-SSRS | Change from baseline to end of week 8 | Patients will complete ASCQ-Me survey domains for emotional impact, social impact, stiffness, and sleep as well as Patient Reported Outcome Information System (PROMIS, a non-disease specific patient reported outcome survey system) domains for pain impact, neuropathic pain, nociceptive pain, cognitive function, gastrointestinal distress and anxiety.^66^ Patients will complete the Leed’s Assessment of Neuropathic Symptoms and Signs (LANSS_ at the beginning and end of study. LANSS is a validated scale of pain quality questions with a scale of 0-24 in which a score of 12 or more defines the presence of neuropathic pain which has been previously used to define neuropathic pain in patients with SCD.^67,68^ The Prodromal Questionaire - Brief is a short psychiatric survey validated to assess for early symptoms of psychosis and the Columbia Suicide Severity Rating Scale (C-SSRS) is a validated measure of suicidality.^59,60^ Both will be administered at each office visit. |
| Opioid Consumption in average daily oral morphine equivalents | Change from baseline to end of week 8 | Opioid use will be calculated using average daily morphine-milligram equivalents based on medications dispensed as documented in the New York State electronic prescribing monitoring program. |

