## 4.2 Scientific Rationale for Study Design

People with sickle cell disease (SCD) have chronic pain from multiple sources^2,3,15^ Inflammation is a driver of pain, end organ damage and early mortality in SCD.^16^ Tetrahydrocannabinol (THC) is a partial agonist for cannabinoid receptors (CB1 and CB2), and has been shown to be effective for the treatment of chronic pain and neuropathic pain in conditions such as cancer and multiple sclerosis.^6,17,18^ There is also evidence from murine models of SCD that CB1 agonists can reduce signs of chronic and neuropathic pain as well as inflammatory cytokines that are important in pain development in SCD.^3,4,19^ The proposed research is built on the scientific premise that dronabinol, an FDA-approved synthetic THC medication may treat chronic pain in SCD and reduce inflammation, and therefore is a promising agent for either the treatment of chronic pain or for treatment of the disease directly through reduction of inflammation.

Randomization will be done 1:1 to dronabinol or placebo in blocks of four, stratified by pain type (neuropathic or not) and past-year cannabinoid use (yes or no). Randomization will be done by the pharmacy. Neuropathic pain will be defined by LANSS score >12. Past-year cannabis use will be defined by self-report of any cannabinoid use (medical, illicit, or cannabidiol containing (CBD) products) in the past year. Based on our prior experience as well as the experience of others, we expect 50% to have neuropathic pain and 50% to have past-year cannabis use after excluding frequent cannabis users.^9,40,61^

The treatment duration will be 8 weeks. Studies of cannabis for the improvement of neuropathic pain in other diseases have ranged in duration from 2 to 26 weeks. Another important component of chronic pain in SCD is chronic inflammation. Changes in inflammatory markers can also take weeks to occur, in studies of acute infections markers of inflammation such as CRP can take up to 6 weeks to normalize.62 Therefore, a study aimed at improving chronic pain in SCD or reducing inflammation should be done over weeks to months. We have chosen 8 weeks which we expect will be long enough to detect efficacy in pain and inflammatory outcomes and identify adverse effects.

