### 9.4.5 Baseline Descriptive Statistics

Intervention groups will be compared on baseline characteristics, including demographics and laboratory measurements, using descriptive statistics.

Though we expect to balance important potential confounders of prior history of cannabis use and neuropathic pain between the two groups via randomization, we will examine whether these differ by randomization group and baseline or over the intervention period. If there are differences between groups, we will include these variables in models.

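### The primary rank-sum test is valid but leaves out the randomisation strata and uses baseline only by subtraction, and any adjusted treatment effect would rest on data-driven covariates

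*Protocol*

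**What the plan says.** Section 9.4.2 frames the primary comparison as a difference in changes: "Median change from baseline of patients on dronabinol will be compared to median change from baseline of patients on placebo". The test is named: "Comparisons of change from baseline to end of study between patients on placebo and dronabinol will be done using a Rank Sum test". No covariate or stratification is attached to it. The stated reason for using change is to allow for baseline differences in the cause and severity of pain.

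Randomisation, by contrast, is "stratified by pain type (neuropathic or not) and past-year cannabinoid use (yes or no" in Section 4.2, and Sections 4.1 and 6.3 also stratify on these two factors.

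Covariates come in by three routes:
- Sections 9.4.2 and 9.4.3: "A backward stepwise multivariate regression analysis will be performed to assess for covariates associated with the primary and secondary outcomes".
- The same sections add a regression to see whether covariates linked to outcome differ significantly between the arms.
- Section 9.4.5, on prior cannabis use and neuropathic pain: "we will examine whether these differ by randomization group and baseline or over the intervention period", and then "If there are differences between groups, we will include these variables in models".

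The neuropathic stratum is defined two ways. Section 4.2 has "Neuropathic pain will be defined by LANSS score >12", and Section 6.3 uses the same cut. Section 3 says that "a score of 12 or more defines the presence of neuropathic pain".

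**The concern.** Stratifying the randomisation and measuring the outcome at baseline both buy precision, but only if the analysis uses them. Subtracting baseline is full adjustment only when the slope of week-8 score on baseline is 1. At any other slope, a change score carries variance that a covariate would remove. With about 56 completers and a decision on a phase III proposal to follow (Section 2.3.3), that matters.

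The second problem is the adjusted result. Backward selection followed by an ordinary test of treatment gives a standard error that ignores the selection. Entering the strata only when an imbalance is seen makes the model depend on the allocation that happened to occur. Together these rules allow several adjusted answers, and none is fixed in advance.

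The third problem is timing. The schedule of activities has LANSS only at baseline and week 8, and change in LANSS is a secondary endpoint. If the phrase in Section 9.4.5 about the treatment period covers neuropathic status, the only LANSS value available is a post-randomisation one that the drug might alter. Adjusting for it could remove part of the treatment effect.

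**Working it through.** **Inputs from Section 9.2:** difference 5 points, SD of change 6.5, 28 per arm, two-sided 0.05, 20% attrition. **Assumed, because the protocol gives neither:** the correlation r between baseline and week-8 scores, and k, the ratio of baseline SD to week-8 SD.

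**1. The plan's own figure.** The noncentrality is 5 / (6.5 × √(2/28)) = 2.878. A t-test with 54 df then has 80.7% power; the exact requirement is 27.5 per arm, so 28. Attrition: 56 / 0.80 = 70. Both figures reproduce.

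**2. The planned test.** On normal data the rank-sum test has efficiency 3/π = 0.955, so 28 per arm act like 28 × 0.955 = 26.7. Power is 78.8%; a simulation of 20,000 trials gave 78.1%. Reaching 80% takes 28.8, so 29 per arm.

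**3. Baseline as a covariate.** With week-8 SD s:
- variance of change = s²(k² + 1 − 2kr)
- ANCOVA residual variance = s²(1 − r²)
- the first minus the second = s²(k − r)²

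The difference is never negative and vanishes only at r = k. For equal SDs (k = 1) the ratio of ANCOVA to change-score variance is (1 + r)/2. Worked case, r = 0.5 and k = 1: ratio 0.75, residual SD 6.5 × √0.75 = 5.63, noncentrality 5 / (5.63 × √(2/28)) = 3.32, power 90.4%.

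| r | Variance saved, k = 1 | Power, k = 1 | Variance saved, k = 0.8 | Power, k = 0.8 |
|---|---|---|---|---|
| 0.4 | 30% | 92.2% | 16% | 87.0% |
| 0.5 | 25% | 90.4% | 11% | 84.9% |
| 0.6 | 20% | 88.5% | 6% | 83.0% |
| 0.7 | 15% | 86.6% | 2% | 81.4% |
| 0.8 | 10% | 84.6% | 0% | 80.7% |

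The table uses 54 df. Fitting baseline and two strata leaves 51 df and lowers each power by about 0.1 point.

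**4. Strata.** The gain depends on how prognostic they are, which the protocol does not say. In a simulation of 4,000 trials with an assumed 4-point effect of one stratum and r = 0.5, k = 1, power was 75% for the rank-sum test and 90% for ANCOVA with baseline and strata. Under no treatment effect, the rank-sum test rejected in 3.9%.

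**5. Stepwise selection.** Assumed: 13 candidates (baseline, two strata, ten noise variables), retention at p < 0.10, 56 participants, 4,000 trials per setting. The type I error of the treatment term after selection was 6.4% to 7.4%. If the better of the rank-sum and stepwise results were reported, it would be about 8% to 10%. The rank-sum test alone stayed at 3.9% to 5.0%.

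**6. LANSS.** The scale takes values from 0 to 24. A participant scoring exactly 12 is non-neuropathic in Sections 4.2 and 6.3 and neuropathic in Section 3. Scores other than 12 are unaffected.

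**The case against.** The strongest reply is that nothing in the primary test is invalid. It uses baseline through the change score, and for a stated reason. It holds its level, and Section 9.4.1 plans to treat all data as non-normal, which explains a rank method. Choosing ANCOVA is then a matter of efficiency. This stands. A reader might infer that the test ignores baseline or is biased, and the protocol supports neither. The reply does not answer the omission of the strata, since van Elteren and rank ANCOVA methods use them without assuming normality.

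Next, the gain rests on assumed r and k. Entry requires a pain-impact threshold, on a different instrument, which may narrow the baseline spread. That stands too, and the k = 0.8 columns show the result.

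Third, a reader might infer that the stepwise model replaces the primary result. It does not: it follows the named test and is described as a search for associated covariates. The error rates in step 5 therefore show what would happen if a treatment effect were read from such a model; they are not the trial's error rate. A candidate list and retention threshold could also sit in an SAP that is not at hand. But the selection method and the imbalance rule are fixed in the protocol, and neither is labelled exploratory.

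Last, a reader might infer that the protocol plans to adjust for week-8 neuropathic status. The sentence in Section 9.4.5 is garbled, names no week-8 LANSS covariate, and also covers prior cannabis use, which treatment cannot change. Post-randomisation adjustment is one fair reading, not a stated plan.

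**Conclusion.** The point holds as one of efficiency and prespecification. The primary test is valid, at about 78-79% power on normal data. Adjusting for baseline would raise this to about 85-92% for r from 0.8 to 0.4 with equal SDs. With a baseline SD 0.8 of the week-8 SD, it gives 87% at r = 0.4 and adds nothing over the t-test's 81% at r = 0.8. Prognostic strata would add to the gain by an amount the protocol does not let one fix. Any adjusted treatment effect is data-driven as written, and the treatment-period wording leaves post-randomisation covariates possible.

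This does not make the sample size wrong: 28 per arm reproduces for a t-test, and the rank-sum shortfall is one participant per arm. Nor do the documents settle which LANSS cut-off is right. They contradict each other, and that is all that can be said.

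**What to change.** 1. Prespecify one primary analysis of week-8 PROMIS pain impact on treatment, with baseline PROMIS and the two randomisation strata as fixed covariates. Use ANCOVA, reporting the adjusted difference and 95% CI, or rank ANCOVA if the non-normality position in Section 9.4.1 is kept. Retain the rank-sum or a van Elteren test as sensitivity.
2. Remove backward stepwise and imbalance-triggered selection from every treatment-effect estimate in Sections 9.4.2, 9.4.3 and 9.4.5, or label them exploratory. Limit covariates to values recorded at baseline.
3. Reconcile the LANSS cut-off across Sections 3, 4.2 and 6.3. Use the strata as randomised in the model and in the subgroup analyses.

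Items 1 and 2 change analysis wording only: every covariate is already collected, and the sample size need not rise. Item 3 needs more care, because altering the cut-off that defines the stratum changes the randomisation itself. If anyone has already been randomised, their stratum as randomised should stand in the analysis.
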